## Abstract

**Background:** Mortality of patients suffering from critical illness has been dramatically improved with advanced technological development of extracorporeal membrane oxygenation (ECMO) therapy. However, the majority of ECMO-supported patients failed to wean from ECMO therapy. As one of several options, cardiopulmonary rehabilitation serves as effective intervention in the improvement of cardiovascular and respiratory function in various major critical illness. Nonetheless, its role in facilitating ECMO weaning has not yet been explored. The purpose of this study is to investigate the effectiveness of cardiopulmonary rehabilitation on rate of ready for ECMO weaning in ECMO-supported patients (CaRe-ECMO).

**Methods:** The CaRe-ECMO trial is a randomized controlled, parallel group, clinical trial. This trial will be performed in a minimum number of 366 ECMO-supported eligible patients. Patients will be randomly assigned to either: (1) the CaRe-ECMO group, which will be treated with usual care including pharmacotherapy, non-pharmacotherapy, and specific nursing for ECMO therapy and the CaRe-ECMO program; or (2) the control group, which will receive usual care only. The CaRe-ECMO program consists of protocolized positioning, passive range of motion (PROM) training, neuromuscular electrical stimulation (NMES), surface electrical phrenic nerve stimulation (SEPNS), and pulmonary rehabilitation. The primary outcome of the CaRe-ECMO trial is the rate of ready for ECMO weaning at CaRe-ECMO day 7 (refers to 7 days after the CaRe-ECMO program initiation). Secondary outcomes include rate of ECMO and mechanical ventilation weaning, total length in day of ready for ECMO weaning, ECMO weaning and mechanical ventilation, all-cause mortality, rate of major post-ECMO complications, ECMO unit length of stay (LOS) and hospital LOS, total cost for hospitalization, cerebral performance category (CPC), activities of daily living (ADL), and health-related quality of life (HRQoL).

**Discussion:** The CaRe-ECMO is designed to answer the question “whether cardiopulmonary rehabilitation can facilitate weaning of ECMO (CaRe-ECMO).” Should the implementation of the CaRe-ECMO program result in superior primary and secondary outcomes as compared to the controls, specifically the add-on effects of cardiopulmonary rehabilitation to the routine ECMO practice for facilitating successful weaning, the CaRe-ECMO trial will offer an innovative treatment option for ECMO-supported patients and meaningfully impact on the standard care in ECMO therapy.

**Clinical Trial Registration:**
ClinicalTrials.gov, identifier: NCT05035797.

## Introduction

Recent improvements in technology have created extra chances for lifesaving, i.e., using extracorporeal membrane oxygenation (ECMO) as a bridge to win over time for the body and medical strategies struggling with critical illness (1). Patients with acute cardiac, pulmonary, or cardiopulmonary failure who have failed conventional treatment appeared to benefit from ECMO therapy (2). However, this population is often exposed to prolonged immobilization, which may lead to multiple complications and impaired physical function (3). Shortening the sedative course and managing issues such as intensive care unit (ICU)-acquired weakness and critical illness-induced cardiopulmonary function impairment should take priority, as this can greatly impact the post-ECMO prognosis. In this context, attention toward enhancing ICU recovery, reducing complications, and improving functional prognosis has started to be shifted to ECMO-supported patients (4). Upon this perspective, early rehabilitation is recommended to be applied in this population.

The general aim of early rehabilitation for critical illness is to improve or maintain cardiopulmonary function, which encounters the requirement of ECMO-supported patients (5). There is a variety of early rehabilitation techniques that may benefit patients with critical illness (6). However, due to the huge difficulties in the application of early rehabilitation in ECMO-supported patients, only a few evidence has been published (4, 7). Considering their pathophysiological condition, regardless of venovenous ECMO (VV-ECMO) or venoarterial ECMO (VA-ECMO), cardiopulmonary rehabilitation is hypothesized to compensate cardiopulmonary function of patients and consequently speed up the recovery process after the emergency period (normally after 72 h) (8). For instance, cardiac output and maximal oxygen uptake were proven to increase after one subtype of cardiopulmonary rehabilitation in intubated, sedated patients confined to bed in the ICU (9).

Upon the above rationale, the upcoming question is that what benefits of cardiopulmonary rehabilitation can be delivered to ECMO-supported patients. For clinicians, ECMO weaning is particularly challenging and annual ECMO mortality has been reported to be approximately ranged 40–70% (10, 11). According to our experience, delayed ECMO weaning also demonstrated worse functional prognosis and impaired health-related quality of life (HRQoL). Previous studies have documented that rate of mechanical ventilation weaning was improved in patients received early rehabilitation intervention, while its effectiveness in ECMO weaning remains unclear (12). Indeed, the successful weaning of ECMO is complex and multifactorial (13). ECMO weaning at the earliest possible time would be expected to improve outcomes, reduce cost, and optimize functional prognosis (14). This inspires us to hypothesize that if the medical rationale is based on its assumed benefits on cardiac function and oxygenation, then cardiopulmonary rehabilitation may subsequently contribute to earlier weaning of ECMO. Our perspective is to provide solutions with the application of cardiopulmonary rehabilitation and convert the aforementioned physiological changes (e.g., increased cardiopulmonary function) into patient-oriented outcomes (e.g., earlier weaning of ECMO and increased rate of ECMO weaning).

Considering the limited evidence in this aspect, ongoing innovation must move from guessing to exploring the effectiveness of cardiopulmonary rehabilitation through an adequately powered trial. Therefore, we design this multidisciplinary randomized controlled trial (RCT) to answer the following clinical question—can cardiopulmonary rehabilitation facilitate weaning of ECMO (CaRe-ECMO)? The results of this trial may subsequently provide innovative treatment solution, specifically the add-on effects of cardiopulmonary rehabilitation to the routine clinical practice for further successful weaning of ECMO.

## Methods/Design

### Trial Design

The CaRe-ECMO trial is a pragmatic, multidisciplinary, randomized controlled, parallel group, clinical trial. Table 1 shows the overview of the trial registration information. The trial protocol was developed according to the Consolidated Standards of Reporting Trials (CONSORT) statements for pragmatic trials and non-pharmacological treatment interventions (15, 16).

**Table 1 T1:** The WHO trial registration data set for the CaRe-ECMO trial.

**Data category**	**Information**
Primary registry and trial identifying number	ClinicalTrials.gov Registry number: NCT05035797
Date of registration in primary registry	01 September 2021
Secondary identifying numbers	N/A
Trial protocol version	Version 1
Source(s) of monetary or material support	Nanjing Municipal Science and Technology Bureau
Primary sponsor	Nanjing Municipal Science and Technology Bureau
Secondary sponsor	N/A
Contact for public queries	XL, [contact]; [name], [contact]; [name], [contact]
Contact for scientific queries	XL, [contact]; [name], [contact]; [name], [contact]
Public title	Can cardiopulmonary rehabilitation facilitate weaning of extracorporeal membrane oxygenation (CaRe-ECMO)? A prospective multidisciplinary randomized controlled trial
Scientific title	Impact of cardiopulmonary rehabilitation on weaning of extracorporeal membrane oxygenation (CaRe-ECMO): A prospective multidisciplinary randomized controlled clinical trial
Countries of recruitment	China
Health condition(s) or problem(s) studied	Rate of ECMO weaning in critical care patients supported with ECMO
Intervention(s)	Active comparator: Usual care, ECMO and cardiopulmonary rehabilitation
Key inclusion and exclusion criteria	Placebo comparator: Usual care and ECMO
	Ages eligible for study: aged 18yr or order
	Sexes eligible for study: both
	Accepts health volunteers: No
	Inclusion criteria: see “Eligibility and withdrawal criteria” section, and Tables 2, 3
	Exclusion criteria: see “Eligibility and withdrawal criteria” section, and Tables 2, 3
Study type	Type: Pragmatic, multidisciplinary, randomized controlled, parallel group, clinical trial
	Allocation: Simple randomization
	Intervention model: Parallel assignment
	Masking: Assessor, physician, data analyst, and statistician blinded
	Primary purpose: Prevention and improvement
	Phase: N/A
Date of first enrollment	Not yet started
Target sample size	366
Recruitment status	Not yet started
Primary outcome(s)	Rate of ready for ECMO weaning at CaRe-ECMO Day 7
Key secondary outcomes	Rate of ECMO weaning, total length of ready for ECMO weaning, total length of ECMO weaning, rate of mechanical ventilation weaning, total length of mechanical ventilation, all-cause mortality, rate of major post-ECMO complications, ECMO Unit LOS, total hospital LOS, total cost for hospitalization, CPC, ADL, and HRQoL

*CaRe-ECMO, cardiopulmonary rehabilitation on extracorporeal membrane oxygenation; LOS, length of stay; CPC, cerebral performance category; ADL, activities of daily living; HRQoL, health-related quality of life*.

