### Trial Setting

The CaRe-ECMO trial will be mainly conducted in the Department of Emergency Medicine, the First Affiliated Hospital of Nanjing Medical University (a 3,700-bed primary referral hospital in Nanjing, Eastern China), who is capable to provide ECMO therapy for ~200 critical care patients annually. Clinicians from the Department of Emergency Medicine are required to have training certifications in ECMO therapy and at least 5-year therapeutic experience in management of critical care patients supported with ECMO. The Department of Rehabilitation Medicine will mainly be responsible for cardiopulmonary rehabilitation delivery. Clinicians from both the departments will collaborate on cardiopulmonary rehabilitation prescription. Therapists are required to have a certified degree in cardiopulmonary rehabilitation and at least 3-year therapeutic experience with critical care patients. The trial coordinating group will implement the CaRe-ECMO program guidelines and standard operation procedures (SOPs) for all the medical staffs via a kickoff meeting to be held in September 2021 (Nanjing, China).

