### Enrollment, Randomization, and Allocation

Eligible patients who meet the eligibility criteria and are provided with ECMO therapy in our Department of Emergency Medicine will be enrolled in the CaRe-ECMO trial. Their guardians will receive a detailed explanation of trial purpose and procedures. The patients will have a same chance to be randomly assigned to the CaRe-ECMO group or the control group. They also will be informed that they have the right to withdraw from the trial at any time of the trial period.

Simple randomization (1:1) will be applied using a computer generated random sequence, which will be independently administered and concealed by the Clinical Research Board from the School of Public Health of Nanjing Medical University (from here on called allocation center). Once a patient has been deemed eligible and the informed consent form has been signed, an independent trial assistant will register the participant, record her/his group allocation, and reveal the group allocation to those delivering the interventions (21). Figure 1 demonstrates the overview of the recruitment, randomization, and allocation based on the CONSORT principle.

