### Interventions

#### CaRe-ECMO Group

Patients in the CaRe-ECMO group will be treated with usual care, ECMO therapy, and cardiopulmonary rehabilitation program. Usual care normally comprises pharmacotherapy, mechanical ventilation, continuous renal replacement therapy (CRRT), intra-aortic balloon pump (IABP), and specific nursing for ECMO therapy and their original injuries, as appropriate. In addition, patients will receive cardiopulmonary rehabilitation from a multidisciplinary team (e.g., clinicians, rehabilitation physicians, nurses, and therapists) who were fully trained to provide care to every ECMO-supported patient when medically appropriate. A core group of clinicians and therapists (e.g., XL, ZS, XC, YZ, YC, and SW) are competent in the use of a screening procedure (e.g., stability of hemodynamic and vital signs, stability of blood coagulation, stability of homeostasis, stability of mechanical ventilation, stability of ECMO flows, and stability of cannulation position and tightness) to determine appropriateness and safety for cardiopulmonary rehabilitation delivery according to the experience from the University of Maryland Medical Center (4). Detailed daily eligibility screening flowchart for cardiopulmonary rehabilitation is shown in Figure 2. Once the patients pass the screen, the therapists will proceed to provide protocolized cardiopulmonary rehabilitation program, which encompasses five evidence-based components according to literature review: (1) positioning; (2) passive range of motion (PROM) training; (3) neuromuscular electrical stimulation (NMES); (4) surface electrical phrenic nerve stimulation (SEPNS); (5) respiratory proprioceptive neuromuscular facilitation (PNF) techniques; and (6) airway clearance techniques (22–24). Detailed content and protocol are given in Table 4. It should be emphasized that hemodynamic and vital signs, ECMO flows, and cannulation position and tightness will be continuously monitored during each rehabilitation session. In case any adverse events occur, cardiopulmonary rehabilitation session will be discontinued. Corresponding reasons for discontinuous and exact length of therapy will be recorded.

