**Figure 2 F2:**
[figure not shown]
Eligibility screening flowchat for cardiopulmonary rehabilitation. ECMO, extracorporeal membrane oxygenation.

**Table 4 T4:** Detailed content and protocol of cardiopulmonary rehabilitation.

**Cardiopulmonary rehabilitation**	**Components**	**Instructions**	**Duration and frequency**	**Rationale**
Positioning	Semi-reclining positioning (30°)	Nurse-assisted position change	Every 2 h	Improve oxygenation (25)
	Left or right lateral positioning (45°) Prone positioning			Improve ventilation/perfusion ratio of the lower part of lung (26) Improve oxygenation (27)
PROM training	PROM training for shoulder joint, elbow joint, wrist joint, hip joint, knee joint, and ankle joint	Therapist-assisted multidimensional movement of joints within normal ROM	20 min per session 1 session per day	1. Maintain joint mobility 2. Prevent contractures 3. Compress peripheral vessels to avoid thrombosis
NMES	NMES (Ruiyi S4, Nanjing Vishee Medical Technology Corporation, Nanjing, China) for triceps brachii, extensor carpal muscles, quadriceps, and tibialis anterior	1. Allocation of electrodes: surface electrodes attached to the motion points of muscles 2. Allocation confirmation: obtain a palpable muscle contraction of the targeted muscle 3. Stimulation parameters: pulse frequency of 40–60 Hz, pulse width of 0.2–0.4 ms, and rectangular, intermittent, bidirectional current	20 min per session 1 session per day	1. Maintain muscle mass, muscle strength 2. Prevent disuse atrophy 3. Compress peripheral vessels to avoid thrombosis
SEPNS	SEPNS (Diafun EDP, Arahelio Group, Guangzhou, China) for Diaphragm	1. Allocation of phrenic nerve: ultrasound scanning on supraclavicular region to identify phrenic nerve which is on the surface of anterior scalene muscle 2. Allocation confirmation: after the surface electrodes attachment, successful SEPNS can be confirmed with ultrasound imaging (M-mode) both at breathing and breath-hold phases reflecting changes of bilateral diaphragmatic thickness and mobility as compared to with no SEPNS 3. Stimulation principles and parameters: in synchrony with mechanical ventilation, pulse frequency of 40–60 Hz, pulse width of 0.2–0.4 ms, and rectangular, intermittent, bidirectional current	20 min per session 1 session per day	Prevent diaphragmatic ICU-acquired weakness

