### Outcome Measures

#### Primary Outcome

The primary outcome of the CaRe-ECMO trial is the rate of ready for ECMO weaning at CaRe-ECMO day 7. It means that rate of ready for ECMO weaning will be calculated 7 days after cardiopulmonary rehabilitation delivery. Checklists to define ready for ECMO weaning (hereafter called ready for ECMO weaning checklists), either for VV-ECMO or VA-ECMO, have been prepared according to literature review and shown in Tables 5, 6 (20, 28). A fixed medical staff will be responsible for checkouts of listed items daily. Eligible patients defined as ready for ECMO weaning reveal the fulfillment of all the items in the checklists. Date of ready for ECMO weaning will be recorded and the rate of ready for ECMO weaning at CaRe-ECMO day 7 will be calculated.

**Table 5 T5:** Ready for VV-ECMO weaning checklist.

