### Blinding

Trial assistants from the allocation center responsible for randomization will be blinded to patients in both the groups. Each cardiopulmonary rehabilitation session provided by the therapists will be sheltered with a curtain. In the control group, an optimization procedure will be imitated as closely as possible, while no cardiopulmonary rehabilitation will be provided. This action may be helpful to blind the clinicians and nurses and mitigate any bias. Assessors, data analysts, and statisticians will be blinded to group allocation.

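### Table 1 lists physicians as blinded, but the protocol has clinicians prescribing, screening for and helping to deliver the rehabilitation, and the Blinding section does not support the claim

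*Protocol article*

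**What the plan says.** **The claim.** The registration data set in Table 1 (Trial Design) reads "Masking: Assessor, physician, data analyst, and statistician blinded", without qualification.

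**Who does what.**
- Trial Setting: "Clinicians from both the departments will collaborate on cardiopulmonary rehabilitation prescription". The two departments are Emergency Medicine, which provides the ECMO therapy, and Rehabilitation Medicine.
- CaRe-ECMO Group: "patients will receive cardiopulmonary rehabilitation from a multidisciplinary team (e.g., clinicians, rehabilitation physicians, nurses, and therapists". A core group of clinicians and therapists "are competent in the use of a screening procedure" to decide whether rehabilitation is appropriate and safe; Figure 2 is described as a daily flowchart.
- Enrollment, Randomization, and Allocation: a trial assistant will "reveal the group allocation to those delivering the interventions".
- Table 4: positioning is a "Nurse-assisted position change" every 2 h, and airway clearance may be given by a therapist, a nurse or a device.

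**What the Blinding section offers.** Sessions given by therapists take place behind a curtain, and a procedure is imitated in the control group without rehabilitation. Of this it says "This action may be helpful to blind the clinicians and nurses and mitigate any bias". Its closing sentence states blinding outright for assessors, data analysts and statisticians only.

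**Who scores the primary outcome.** Primary Outcome: "A fixed medical staff will be responsible for checkouts of listed items daily". That section does not say whether this person is the blinded assessor.

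**The concern.** A clinician who prescribes rehabilitation for a patient knows that patient's arm, so Table 1 appears to claim a protection that the design does not have. Unblinded delivery is ordinary in a rehabilitation trial and is no fault in itself. The fault is to state physician masking in the registration data set, where readers will look for it when judging risk of bias.

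The claim matters because of the endpoint. Readiness for weaning is a dated call made from a checklist. Most items are numeric thresholds, but some are judgements, and readiness also requires a weaning trial. If the person making the call, or those shaping the inputs, know the arm, readiness could be called more often or earlier in one group.

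**Working it through.** The masking claim rests on no stated figure, so the check is a comparison of the document's own statements, followed by one illustration under assumptions.

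**1. Each masked role in Table 1 against the rest of the article**

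| Role in Table 1 | Blinding section | Roles stated elsewhere | Result |
|---|---|---|---|
| Assessor | Blinded, stated outright | Checklist scorer is described only as fixed medical staff | Not contradicted; link to the scorer not stated |
| Physician | Measures may be helpful; absent from the firm list | Clinicians prescribe; clinicians and rehabilitation physicians are on the treating team; clinicians screen; allocation revealed to deliverers | Not supported |
| Data analyst | Blinded, stated outright | Nothing contrary | Stands |
| Statistician | Blinded, stated outright | Nothing contrary | Stands |

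Nurses are not in the Table 1 entry. Their part in positioning, and possibly in airway clearance, bears only on the hedged sentence in the Blinding section.

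**2. Can the curtain and the imitated procedure make the physician entry true?** The curtain covers sessions provided by therapists. It cannot hide a prescription from the clinician who writes it, nor position changes from the nurse who assists them. The imitated procedure could hide the arm from a clinician with no part in prescribing or delivery, but the article does not define such a group. Screening alone need not unblind if controls are screened in the same way, which the article does not say. Prescribing and delivering do unblind.

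**3. Is the endpoint open to influence?** All items must be met.
- Judgement items, Table 5: primary disease controlled or improved, improved imaging, improved function of other damaged organs.
- Judgement items, Table 6: cause of cardiac failure compatible with recovery, improved function of other damaged organs.
- Numeric items, for example: PaO2/FiO2, PaCO2, MAP, lactate and SvO2; in Table 6 also LVEF and VIS.
- Both tables require a weaning trial at Step 4.

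The endpoint is therefore mostly numeric, with some room for judgement.

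**4. Illustration only.** The documents give no size of bias. Assume true readiness of 30% in both arms (the 30% is from Sample Size Calculation), n = 183 per group (the target), and a net shift s in readiness calls towards the CaRe-ECMO group. For a two-sided 5% pooled test of two proportions:

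- p1 = 0.30, p2 = 0.30 + s, p̄ = (p1 + p2)/2
- SE0 = √[2p̄(1 − p̄)/n]; SE1 = √[p1(1 − p1)/n + p2(1 − p2)/n]
- P(reject) = Φ[(s − 1.96·SE0)/SE1] + Φ[(−s − 1.96·SE0)/SE1]

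| s (assumed) | SE0 | SE1 | P(reject) | Patients, s × 183 |
|---|---|---|---|---|
| 0 | 0.0479 | 0.0479 | 0.050 | 0 |
| 0.03 | 0.0486 | 0.0485 | 0.090 + 0.005 = 0.095 | 5.5 |
| 0.05 | 0.0490 | 0.0489 | 0.174 + 0.001 = 0.175 | 9.2 |
| 0.10 | 0.0499 | 0.0496 | 0.518 + 0.000 = 0.518 | 18.3 |

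The first term, rejection in favour of CaRe-ECMO, gives the 9%, 17% and 52% quoted in summary. With 174 per group, both tails together give 9.2%, 16.9% and 49.8%.

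**The case against.** The strongest reply is that this is a narrow reporting inconsistency.

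- **Most of the masking stands.** A reader might infer that the stated masking does not exist at all. The documents do not support that: three of the four entries are stated again in the Blinding section, and nothing contradicts them for analysts and statisticians. This part of the reply holds.
- **There is a real attempt at clinician masking.** The imitated control procedure, with the curtain, must be credited. It is a partial measure, and the article itself only hopes that it helps.
- **The word physician may mean only those outside the rehabilitation team.** The article does not say so. It has clinicians of both departments prescribing, without exception, and names rehabilitation physicians on the treating team.
- **The scorer may well be the blinded assessor.** That is a natural reading, and staffing detail often sits in a full protocol. It means that an unblinded scorer is not shown. It does not repair the physician entry.
- **The endpoint is mostly objective.** A favourable judgement cannot produce readiness if a threshold or the weaning trial fails, and the Discussion says that the checklists are there to limit performance bias. This limits the risk without removing it.
- **Who sets ventilator, ECMO and vasoactive values is not stated.** That unblinded staff control the numeric items is an inference, and the point does not rest on it.
- **The shifts in the illustration are assumed.** They are the power of a test at chosen differences. A 10-point shift would be two-thirds of the planned difference of 15 points (30% to 45%).

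**Conclusion.** The physician-masking entry in Table 1 is unsupported. The document's own allocation of tasks has clinicians prescribing, screening for and helping to deliver the rehabilitation, and its Blinding section declines to assert what the table asserts. This is a contradiction within the article, not a detail left to a fuller document.

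The consequence is that protection against bias is overstated for a primary endpoint with some judgement items. A reader might go further and infer that the primary result will be biased. The documents do not show that: assessor blinding is stated, the scorer's identity is open, most items are numeric, and no bias size can be derived. The rejection rates show what would follow from assumed shifts, all in one direction with no true effect. They are not an estimate for this trial.

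The correction should be made, because Table 1 reports that enrollment had not started and the change is small.

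**What to change.** 1. **Table 1 and Blinding section, in the same terms.** State that clinicians who prescribe, screen for or deliver rehabilitation, and the therapists and nurses who deliver it, are not blinded; that the curtain and imitated control procedure are a partial measure; and that assessors, data analysts and statisticians are blinded. Align the registry record if it carries the Table 1 entry.
2. **Primary Outcome section.** Specify that the fixed medical staff who score Tables 5 and 6 are the blinded assessor, drawn from existing staff with no role in prescribing, screening for or delivering rehabilitation, and that they score outside sessions in both arms.

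A sensitivity analysis restricted to measured items is optional. It would remove the judgement items, but the measured values may also reflect care by staff who know the arm, so it does not replace an independent blinded scorer.

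**Cost.** Wording in two places of the article, possibly a registry update, and a duty-assignment rule for existing staff. The sample size and patient care do not change. The downside is that the stated masking will look less favourable.
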